#### Exclusion criteria

Inability to follow RMT instructions or complete questionnaires for our study due to cognitive impairment.A COPD exacerbation, chronic heart failure, history of stroke, high-risk cardiopulmonary disease or orthopaedic disease within the previous 4 weeks.Diagnosis of lung cancer or history of thoracoabdominal surgery.A body mass index (BMI) of ≥ 30.Inpatients.Pleural disease or thoracic deformity.Visual or hearing impairment.Receiving medication that may cause cognitive impairment.Completed pulmonary rehabilitation within the last 12 months or currently participating in an exercise programme. Severe cognitive impairment/dementia (Montreal Cognitive Assessment score < 17) or other diagnosed neuropsychiatric symptoms.

### Recruitment and selection

This study will rely on COPD patients associated with the respiratory department of Anqing Hospital of the People’s Liberation Army Navy and COPD combined with CI patients in the surrounding community of this hospital for sample recruitment to ensure adequate sample size, ease of implementation of the relevant experimental protocol and to reduce sample attrition. Recruitment for This study in this experiment will take place on 1 January 2024, and on 1 February 2024, the 12-week experimental period will officially begin. Relevant medical data and screening will be evaluated by a medical professional. Subjects will also sign an informed consent form indicating their voluntary participation in the trial. The protocol follows the Standard Protocol Items: Recommendations for Interventional Trials (SPIRIT) 2013 [27]. A brief SPIRIT flow diagram is shown in Table 2. A populated SPIRIT checklist is provided in the Additional file.

**Table 2 Tab2:**
[figure not shown]
Tabulated summary of the study schedule

### Randomisation and blinding

All participants in the experiment were randomised into groups and sequences will be generated by the random sequence generator (www.random.org) and randomly distributed to the participants by the experimental recruitment team by sealing the sequences in envelopes. The participants were then divided into HG, BDJ and CG groups in a 1:1:1 ratio. Assessors for the cognitive and physical tests were formally blinded, while participants and trainers were not blinded. The data processor will also be blinded to the processing of data reports collected during the pre-, mid- and post-experimental periods and will be required not to communicate with the data processor about the experimental protocol to ensure objective and reliable data analysis. If a patient is unable to accept the group to which he or she has been randomly assigned due to a medical condition, the recruiting team, in collaboration with the physician, will conduct a comprehensive assessment of the patient and document the event. It is also possible to transfer patients to other groups to continue the pulmonary rehabilitation intervention according to their wishes. However, this person’s data on the relevant indicators were not counted in the data analysis pool for this experiment.

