### Intervention

#### Head-down strong abdominal breathing group (HG)

Patients will have a week before the experiment to focus on understanding and learning the head-down strong abdominal exercise to ensure that the participants in the group can perform the relevant movements in a standard way during the formal experiment. During the experiment, head-down strong abdominal breathing will be performed in accordance with the experimental requirements, from easy to difficult, and the participant will be asked to empty their bowels and to perform the head-down strong abdominal breathing at least 1 h after a meal, and to complete the training in one session. The intensity of the intervention was 40 min three times per week, including 5 min of warm-up and acclimatisation at the beginning of the exercise, 30 min of head-down strong abdominal breathing, 5 min of stretching and relaxation, with a respiratory rate of 25 breaths/min (metronome cue), and head-down training on an inverted upside-down dual-purpose exercise machine (Patent No. 201821510570.5) at an inclination angle of − 30°. The intervention period was 12 weeks. Figure 2 shows the field pictures of the carotid blood flow characteristics and the factors influencing it in different positions in young people studied by the head-down strong abdominal breathing in the early stage of this research project [28].This study will also use this inverted upside-down dual-purpose exercise machine to perform head-down strong abdominal breathing exercises.

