#### Control group (CG)

Patients do not undergo any systematic exercise rehabilitation and only undergo a routine medication programme.

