### Statistical analysis

All statistical analyses were performed using SPSS v.27.0. Data are presented as means and standard deviations or proportions. Standard error of the mean (± SEM) was used to look at trends between cardiorespiratory and cerebrovascular changes during exercise and was more appropriate than SD, which was used to indicate the variability of data between patients. Statistical significance of differences between groups was assessed by analysis of variance, paired *t*-test and chi-square test. In addition, one-way ANOVA with repeated measures was used to determine statistically significant differences between the different percentiles of total exercise duration for oxy-Hb, Deoxy-Hb, Total-Hb, TSI, and blood oxygen saturation during exercise. Multiple comparisons using LSD honestly significant difference post hoc procedure to determine pairwise differences. Pearson’s correlation coefficient was used to assess the bivariate relationship. Multiple linear regression models were used to assess potential relationships between determinants of cognitive impairment and changes in cerebral oxygen utilisation and cerebral haemoglobin volume. Missing values in the data will be statistically analysed by multiple interpolation. The level of bivariate significance was set at *P* ≤ 0.05.

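### The transfer rule drops randomised patients from the analysis for a reason that depends on their arm, so the comparison may be biased, probably towards HG

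*Protocol article*

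**What the plan says.** The rule stands in the protocol article under Randomisation and blinding. Participants are allocated to "HG, BDJ and CG groups in a 1:1:1 ratio", which for 81 patients is 27 per arm. The trigger comes next: "If a patient is unable to accept the group to which he or she has been randomly assigned due to a medical condition". Such a patient is assessed by the recruiters together with the physician, and the event is documented. Then: "It is also possible to transfer patients to other groups to continue the pulmonary rehabilitation intervention according to their wishes". The last sentence says that this person's "data on the relevant indicators were not counted in the data analysis pool for this experiment". The same section states that "participants and trainers were not blinded".

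The arms ask different things of the patient. HG involves "head-down training on an inverted upside-down dual-purpose exercise machine", while control patients "only undergo a routine medication programme".

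On missing data, Statistical analysis says: "Missing values in the data will be statistically analysed by multiple interpolation". I read this as multiple imputation. No section says that patients are analysed in the group to which they were randomised.

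**The concern.** A randomised comparison is fair because the arms differ only by chance at allocation. A rule that removes patients afterwards keeps that property only if removal is unrelated to the arm or unrelated to the outcome. Here removal is tied to the arm, because the question asked is whether the patient can take that particular treatment. A medical trigger also makes it plausible that the removed patients differ in prognosis.

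The rule decides who enters every between-group comparison, including the primary one on prefrontal oxygenation. If the scheduled assessments of transferred patients are not made, their outcomes cannot be recovered later.

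**Working it through.** The plan gives no figure on this point, so there is none to reproduce. The check has two parts.

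**1. Following the rule through each arm**

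Take one patient with a condition that rules out training at −30° on the inversion machine.

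- Randomised to HG: cannot accept the group, may be transferred, and leaves the analysis.
- Randomised to BDJ: leaves only if the condition also prevents those exercises. (The BDJ section lists head-down breathing as its session content, at odds with the qigong movements it selects. Those passages must be reconciled, but on either reading BDJ is an exercise arm.)
- Randomised to control: there is no training to be unable to accept, so the patient stays in.

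The same patient is kept or deleted according to the allocation. Three other provisions could have repaired this, but none does:

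- Multiple imputation fills missing values of patients in the analysis. It does not bring back people removed from it.
- The Safety section seeks an assessment from patients who withdraw, but does not mention transferred patients.
- The Adherence section records receipt of another intervention, but does not say how such patients are analysed.

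**2. Illustration of size (all inputs except 27 per arm are assumed)**

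Suppose there is no true effect, the outcome has SD 1, the k least tolerant of 27 HG patients are removed, and no one is removed from control. Tolerance is standard normal with correlation ρ to outcome.

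- Fraction removed: q = k/27, with z the q-quantile of the standard normal.
- Mean tolerance of those retained: λ = φ(z)/(1 − q).
- Shift of the HG mean: ρ × λ.
- Variance of the retained HG outcomes: v = 1 − ρ²λ(λ − z).
- Standard error of HG minus control: SE = √(v/(27 − k) + 1/27).
- Two-sided rejection rate: Φ(shift/SE − 1.96) + Φ(−shift/SE − 1.96).

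For k = 3 and ρ = 0.5: q = 0.111, z = −1.221, λ = 0.213, shift = 0.5 × 0.213 = 0.107 SD. Then v = 1 − 0.25 × 0.213 × 1.434 = 0.924, SE = √(0.924/24 + 1/27) = 0.275, and the rejection rate is 6.7% against a nominal 5%.

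| Removed from HG | λ | Shift, ρ = 0 | Shift, ρ = 0.3 | Shift, ρ = 0.5 | Rejection rate, ρ = 0.5 |
|---|---|---|---|---|---|
| 1 of 27 | 0.084 | 0 | 0.03 | 0.04 | 5.3% |
| 3 of 27 | 0.213 | 0 | 0.06 | 0.11 | 6.7% |
| 4 of 27 | 0.271 | 0 | 0.08 | 0.14 | 7.8% |
| 6 of 27 | 0.383 | 0 | 0.12 | 0.19 | 10.4% |

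At ρ = 0 the rejection rate stays at 5.0%. Six of 27 is 22%, above the 10–15% total attrition that the plan allows, so the last row is an outer case. Analysing all 27 per arm as randomised removes this selection shift.

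**The case against.** The best case for the plan is that the rule will seldom apply. It needs a medical condition and a documented assessment with the physician. Eligibility already excludes recent exacerbation, high-risk cardiopulmonary disease and orthopaedic disease. HG patients have a learning week, and the Discussion says that angle and respiratory rate are assessed beforehand and the angle adjusted to the patient. The wording also suggests a problem at or near allocation rather than intolerance weeks later. All of this limits the number of transfers and so the likely size of any bias. It does not repair the rule: even at the first session the patient is already randomised and knows the arm, and a medical filter makes removal more likely to be prognostic.

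A reader might infer more than the documents support:

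- *That the bias certainly favours HG.* The rule covers all arms, BDJ may lose patients too, and nothing states that control stays complete.
- *That the expected adverse events belong to HG.* The list of dizziness, headache and nausea under Adherence and adverse events names no arm and is not linked to transfer.
- *That a patient may leave the analysis by wish alone.* On the natural reading, the wish guides the transfer that follows medical inability; it is not a second trigger.
- *That observed outcomes are thrown away while unseen ones are imputed.* No section says that transferred patients are assessed.
- *That the bias is a stated share of the design effect.* That would read f = 0.25 as a one-way group effect, for which 80% power needs 159 patients, not the planned 69. The base is too uncertain for a percentage.

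**Conclusion.** Wrong as written. The article states an explicit post-randomisation exclusion, so this is not a detail left to an unseen analysis plan, and nothing else in the article restores analysis by randomised group. This conclusion rests on the text alone.

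Direction and size are less certain. Bias towards HG is the more probable direction, because HG requires inversion training and control offers little that a medical condition could prevent. That is an inference. With 3 of 27 HG patients removed the illustration gives 0 to about 0.1 SD, and it depends on the assumed number of transfers, on the least tolerant being the ones removed, on a tolerance–outcome correlation between 0 and 0.5, and on no losses from control. The need for a change comes from the rule itself, not from these figures.

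**What to change.** Replace the last sentence of the rule with wording such as: *Every randomised patient is included in the primary comparison in the group to which he or she was randomised, whatever intervention was received. Transferred patients are invited to the scheduled week-6 and post-intervention assessments. Outcomes that are still missing are handled by the multiple imputation described under Statistical analysis. An analysis without transferred patients is reported only as a labelled sensitivity analysis.*

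The medical assessment, its documentation and the possibility of transfer stay as they are. No new method is needed, since the imputation is already planned. The cost is a few additional assessments and some dilution of the estimated effect if patients switch arms.

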### Intervention

#### Head-down strong abdominal breathing group (HG)

Patients will have a week before the experiment to focus on understanding and learning the head-down strong abdominal exercise to ensure that the participants in the group can perform the relevant movements in a standard way during the formal experiment. During the experiment, head-down strong abdominal breathing will be performed in accordance with the experimental requirements, from easy to difficult, and the participant will be asked to empty their bowels and to perform the head-down strong abdominal breathing at least 1 h after a meal, and to complete the training in one session. The intensity of the intervention was 40 min three times per week, including 5 min of warm-up and acclimatisation at the beginning of the exercise, 30 min of head-down strong abdominal breathing, 5 min of stretching and relaxation, with a respiratory rate of 25 breaths/min (metronome cue), and head-down training on an inverted upside-down dual-purpose exercise machine (Patent No. 201821510570.5) at an inclination angle of − 30°. The intervention period was 12 weeks. Figure 2 shows the field pictures of the carotid blood flow characteristics and the factors influencing it in different positions in young people studied by the head-down strong abdominal breathing in the early stage of this research project [28].This study will also use this inverted upside-down dual-purpose exercise machine to perform head-down strong abdominal breathing exercises.

**Fig. 2 Fig2:**
[figure not shown]
Experimental field diagram of the inverted trainer in different positions

#### Eight Duan Jin Group (BDJ)

The two sets of movements in the Eight Duan Jin of Fitness Qigong, which have a regulatory effect on the respiratory function, were selected: “Two hands resting on the sky to manage the three jiao, and left and right opening the bow like a shooting eagle” [29, 30]. Each session is 40 min and consists of a 5-min warm-up adaptation at the beginning of the exercise, 30 min of head-down strong abdominal breathing exercises and 5 min of stretching exercises to relax, three times a week for a 12-week intervention cycle. The main technical movements are shown in Fig. 3.

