With the advent of inversion devices in rehabilitation, more and more people are using such devices for rehabilitation. In a study of head-down training in an elderly population, it was shown that changes in body position had an effect on cerebral blood flow and also led to a reduction in psychological stress and improved sleep quality in the lives of older people [18]. In another study on the magnitude of diaphragmatic excursions in healthy subjects, the optimal change in diaphragmatic excursions was obtained in healthy subjects using a 30° head-down tilt position [19]. Strong abdominal breathing is one type of breathing. Currently, studies exploring MCI in COPD patients through head-down strong abdominal breathing training are rare internationally. Previous studies have found that head-down training has a relatively significant effect on, for example, cerebrovascular function [18], while studies of lung function have found heterogeneity. A review of the relevant literature also revealed that respiratory training can improve cognitive function in COPD patients [20], but the depth of research needs to be further improved. Therefore, this study will explore the cerebral blood flow alteration status through head-down strong abdominal breathing training. We also monitored the status of HbO2 changes in the prefrontal cortex by fNIRS and evaluated the improvement of cognitive function in COPD from multiple perspectives by combining the Overall Cognitive Assessment Scale, the Specific Cognitive Assessment Scale, and the Cognitive Behavioural Ability Level Test [21–23].

The effectiveness of traditional Chinese sports in promoting health is well documented. In particular, the Eight Duan Jin exercises have been shown to improve the respiratory function of the body, mainly by enhancing the elasticity of the diaphragm and increasing the volume of the thorax, thereby increasing the inspiratory volume of the lungs and improving exercise capacity [24, 25]. We compared Fitness Qigong Ba Duan Jin with head-down strong abdominal breathing to verify the effectiveness of head-down strong abdominal breathing in relation to traditional Chinese exercise programmes in improving cognitive function in COPD patients.

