**Fig. 3 Fig3:**
[figure not shown]
Fitness Qigong eight-dan jin selection movements

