Ba Duan Jin is a traditional Chinese sport with a long history, easy to learn and highly effective. The practice of Ba Duan Jin requires no equipment, is not limited by space, and has significant effects on strengthening the body, regulating the movement of qi and blood in the internal organs, and improving respiratory function [46]. Yang et al. [47] concluded from a study of patients with mild COPD that traditional Ba Duan Jin exercises can prevent the deterioration of lung function in COPD and provide a simple, inexpensive, and routine pulmonary rehabilitation measure for patients with mild COPD. This experiment compares the Baduanjin group with the HG group, thus arguing for the effectiveness of the HG training method to be significant.

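### The Ba Duan Jin arm's session is itemised with head-down strong abdominal breathing as its whole 30-minute core, leaving no time for Ba Duan Jin

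*Protocol article*

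**What the plan says.** The BDJ section opens by naming the content of the arm: "The two sets of movements in the Eight Duan Jin of Fitness Qigong, which have a regulatory effect on the respiratory function, were selected". It then sets out the time: "Each session is 40 min and consists of a 5-min warm-up adaptation at the beginning of the exercise", followed by "30 min of head-down strong abdominal breathing exercises and 5 min of stretching exercises to relax", three times a week for 12 weeks. It closes by referring to Fig. 3, whose caption reads "Fitness Qigong eight-dan jin selection movements".

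The HG section gives that arm's session as "5 min of warm-up and acclimatisation at the beginning of the exercise, 30 min of head-down strong abdominal breathing" and 5 minutes of stretching. The session length, weekly frequency and 12-week duration are the same as for BDJ. The HG section adds the delivery details, "with a respiratory rate of 25 breaths/min (metronome cue), and head-down training on an inverted upside-down dual-purpose exercise machine", together with the −30° inclination, a week of learning beforehand, and rules on bowel emptying and time since a meal. None of these is given for BDJ.

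The purpose of having both arms is stated twice. The Introduction says: "We compared Fitness Qigong Ba Duan Jin with head-down strong abdominal breathing to verify the effectiveness". The Discussion says: "This experiment compares the Baduanjin group with the HG group". The section on randomisation and blinding allocates patients to HG, BDJ and control (CG) as three separate groups in a 1:1:1 ratio.

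**The concern.** The BDJ session is introduced as consisting of its listed parts, so the list reads as complete, and its 30-minute core is the experimental exercise instead of the comparator exercise. The section therefore contradicts its own heading and first sentence, and also the comparison that the trial is meant to make.

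What is at stake depends on how the sessions were run.

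- **If the printed text was followed literally,** both active arms had the same named core activity. The HG–BDJ contrast would then no longer compare two kinds of exercise, and BDJ–CG would no longer estimate an effect of Ba Duan Jin. BDJ patients would also have trained head-down without the angle, breathing rate and preparation rules set for HG.
- **If trainers followed the named movements and Fig. 3,** the trial itself is sound on this point. The harm is then a wrong published definition of the comparator, which could mislead anyone who replicates the trial, judges its fidelity or includes it in a synthesis.

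**Working it through.** **Inputs, all from the Intervention section of the protocol article**

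| Item | HG | BDJ as printed |
|---|---|---|
| Session length | 40 min | 40 min |
| Warm-up | 5 min | 5 min |
| Core | 30 min head-down strong abdominal breathing | 30 min head-down strong abdominal breathing |
| Stretching | 5 min | 5 min |
| Frequency and duration | 3 per week, 12 weeks | 3 per week, 12 weeks |
| Ba Duan Jin movements | none | two selected, no minutes assigned |

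**Step 1: reproduce the stated session length.** Warm-up + core + stretching = 5 + 30 + 5 = 40 min in each arm. This agrees with the 40 minutes stated, so the BDJ list is complete.

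**Step 2: time left for Ba Duan Jin as printed.** 40 − (5 + 30 + 5) = 0 min per session.

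**Step 3: dose over the programme.** Sessions = 3 × 12 = 36.

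- Ba Duan Jin as printed: 36 × 0 = 0 h.
- Ba Duan Jin if the 30-minute core belongs to the selected movements: 36 × 30 = 1080 min = 18 h.
- HG core: 36 × 30 = 1080 min = 18 h.

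The corrected reading gives the two active arms equal core doses.

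**Step 4: contrasts affected.** Three arms give three pairwise contrasts. HG–BDJ and BDJ–CG involve the BDJ definition; HG–CG does not.

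**Step 5: which reading was intended.** These features point to Ba Duan Jin as the intended core:

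- the arm's heading;
- the two movements chosen;
- the Fig. 3 caption;
- the comparison described in the Introduction and the Discussion;
- the confinement of the machine, angle, metronome rate and preparation rules to HG.

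Only the one phrase in the time breakdown points the other way, and it matches the HG paragraph in both wording and structure. Nothing in the article describes head-down breathing as a planned addition to BDJ, and the minutes leave no room for both. A copying error is by far the likeliest explanation.

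**The case against.** The strongest reply is that this is a slip which the surrounding text largely resolves. The sentence before it names the movements, the sentence after it points to their illustration, and the rest of the article treats BDJ as a Ba Duan Jin arm. For the sentence to do harm in practice, trainers would have had to ignore all of that and use apparatus specified only for HG. Nothing in the article suggests that they did. The dose figures multiply one wrong phrase by 36 and measure no effect on power, error rate or bias. Figures 1 and 3, Table 2 and the additional file cannot be seen here and may state the content correctly. The article also assigns no minutes to the two movements, so any replacement wording has to come from the investigators.

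Most of this stands as a limit on severity. The intended activity can be inferred, literal delivery is a hypothetical without support in the article, and no size of effect can be claimed. It is also fair to call the faulty sentence the only time breakdown shown for BDJ, because the neighbouring sentences do state part of the content.

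It does not remove the error. The article has not merely left out a detail; it names the wrong exercise for a randomised arm. The sentence is intact running prose, so text extraction does not explain it. A reader can guess which exercise was meant, but must also guess that all 30 minutes belong to it, because no Ba Duan Jin dose is stated anywhere in the text.

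**Conclusion.** The concern holds. As printed, the BDJ session gives 0 of its 40 minutes to Ba Duan Jin and repeats the HG core, which contradicts the comparison the trial sets out to make. The definition underlies two of the three pairwise contrasts; HG–CG is untouched.

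The arithmetic rests only on figures in the article. The 18-hour corrected dose rests on one assumption, that the whole 30-minute core was meant for the two selected movements. How sessions were actually delivered is not shown, so no effect on the results is claimed. On the likeliest reading the damage is confined to the published description of the comparator. It should be fixed because it sits in the operative definition of a randomised arm and is cheap to repair.

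**What to change.** After the investigators confirm what the arm did, replace the head-down breathing phrase in the BDJ section with *30 min of practice of the two selected Ba Duan Jin movements*. The session remains 5 + 30 + 5 = 40 minutes, three times a week for 12 weeks, with its core dose matched to HG.

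The Trial status section expected completion by April 2024 and the article appeared on 30 May 2024, so the change should be issued as a published correction.

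Check the trainers' materials and session records for the BDJ arm. If any session used head-down breathing, report how many as a departure from the intended comparator, and take it into account when interpreting HG–BDJ and BDJ–CG.

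The cost is one corrected phrase and a records check. Sample size and analysis stay as they are.
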